### Intervention

On top of CAU, nurse-assisted eye screening will take place with the Easee test. This e-health tool was introduced to measure visual acuity without any physical eye chart, but instead using a computer, laptop or tablet, and a smartphone. The Easee test was originally developed for measuring visual acuity and spherical and cylindrical refractive errors in adults up to 45 years old. The test is Conformité Européenne marked and is also commercially available via the website of Easee (https://www.easee.online/nl/). A version of the Easee web tool has been tailored to the requirements of the older adults in this cluster RCT. Currently, the test is certified as a class 1 device under the Medical Device Directive 93/42/ECC. Class 2a certification is pending. Easee has an ISO13845 which is monitored and audited by TüV Rheinland, Germany. The software is classified as class A, in accordance with IEC 62304:2006.

The tests will be displayed on the laptop. The smartphone will function as a remote control by which the participant submits input to the laptop screen. If the participant can execute the test by him- or herself, the nurse will merely supervise to ensure correct application. If more assistance is needed, the nurse will provide this. Standard audio instructions guide the nurse and participant through the test. The test will start with four triage questions, which are used to set up a correct referral: (1) Are you diagnosed with any eye disease (such as macular degeneration, cataract, diabetic retinopathy, or glaucoma)? (2) Do you have amblyopia? (3) Did you receive an optometric or ophthalmic consultation within the last 6 months? (4) Did you experience a sudden vision loss or distortion? During the test, both eyes are tested consecutively, covering one eye at a time. The participant will wear his/her spectacles, if present. The participant is presented a sequence of optotypes (i.e., tumbling-E and triangle-circle optotypes) that the participant must correctly identify, in addition to various grate sizes, both near and at a distance. The Amsler grid test is performed to detect any macular problems.

#### Referral and intervention uptake

The results of the eye screening will be checked by an optometrist and will be made available to the participant by letter within 1 week after the screening takes place. This will include a recommendation for a referral, if necessary. Participants will be referred to an optometrist (primary or secondary healthcare). In the Netherlands, primary healthcare provides the first point of contact in the healthcare system, accessible without referral. In the context of our study, primary healthcare encompasses optometrists who typically work at an optical store or at a community health center. Secondary eye care comprises clinical services which need a referral from a GP or primary care optometrist. The criteria for referral can be found in Fig. 2. These criteria were based on the classification of vision impairment of “The International Classification of Disease 11 (2018) of vision impairment” [36], which describes a vision impairment as having a visual acuity worse than 0.5 (20/40) (Snellen). In addition, the driving requirements of the government of the Netherlands [37] were used, where a visual acuity of at least 0.5 (20/40) (Snellen) is required for driving a car. The nurse will discuss the referral with the patient and will check whether the patient has used the referral. If not, additional motivational conversations between the involved community nurse and participant will take place after 2, 4, and 6 weeks. The optometrist who receives the referral will perform an optometric examination according to their usual care and practice guidelines, tailored by the information supplied in our referral. Throughout this RCT, the expenses for these examinations will be reimbursed.

**Fig. 2 Fig2:**
[figure not shown]
Flowchart referral ^a^Snellen visual acuity

#### Reliability online eye screening

Recently, we studied the reliability and feasibility of the online eye screening in patients receiving home healthcare [28]. Forty patients (80 eyes) were included. The following mean differences between the online eye screening and reference tests were found: distance visual acuity 0.02 logMAR, near visual acuity measured with tumbling-E optotypes 0.06 logMAR, and 0.03 logMAR with the triangle-circle optotypes. For distance visual acuity, 75% of the individual data points were within the non-inferiority threshold (± 0.15 logMAR). For near visual acuity, 51% and 58% were within the non-inferiority threshold for the tumbling-E and triangle-circle optotypes, respectively. The results showed negligible to small mean differences between the tests implemented in the online eye screening and the traditional visual acuity measurements. The agreement between tests for macular problems was 75% [28]. The convenience and ease of an online eye screening at home, along with the added support of a trusted community nurse, were cited as the main advantages by participants. However, the study also identified several disadvantages of an online eye screening at home, including the lack of optimal lighting conditions, and the limited scope of the screening. The online eye screening may not be able to detect certain eye conditions that can be identified through more comprehensive examinations performed by eye care professionals. Furthermore, several participants and community nurses commented on the duration of the eye screening, with a mean duration of 42 min. The online eye screening has been adapted, by removing the measurement of refractive error, to shorten the eye screening. To determine whether patients should be referred to an eye care professional, which is the goal of eye screening, visual acuity, and Amsler measurements should suffice.

Previously, the reliability and efficacy of the web-based tool were also tested against traditional subjective manifest refraction by an optometrist (golden standard) in a prospective open-label non-inferiority clinical trial in 200 eyes of 100 healthy volunteers (18–40 years), with a refraction error between -6 and + 4 diopters (non-inferiority criterion 0.5D or less) [38]. Web-based assessment was considered non-inferior to the reference test with an excellent intraclass correlation of 0.92. In addition, uncorrected visual acuity was also similar and significantly improved using the prescription obtained from the web-based tool.

Therefore, it was concluded that web-based eye testing is a valid and safe method for measuring visual acuity and refractive error in healthy eyes [38].

#### Training community nurses

Teams of community nurses, who have been randomized to the intervention group, will be trained to assist patients with the online eye screening. All nurses involved in the eye screening will administer the online eye screening twice with two voluntary participants (e.g., relatives, colleagues, or friends) before they start screening study participants. The training also teaches nurses how to motivate their patients for intervention uptake after referral, by making use of motivational interviewing. Motivational interviewing is an effective way to explore and resolve ambivalence that individuals may have about health behavior, with the goal of promoting positive change [39, 40].

### Care as usual

The intervention and control groups will receive CAU. The control group will not be actively screened with the Easee tool for eye complaints; all necessary care will be provided by the community nurse. It is possible that eye complaints are being discussed spontaneously. These are registered and/or followed up as usual by the nurse and home healthcare organizations.

### Study procedures

Measurements in both groups will take place at baseline (T0) and after 6 months (T1) and 12 months (T2) of follow-up (Table 2). A baseline assessment will take place before randomization. During all assessments, visual acuity measurements and Amsler tests will take place at the participants’ homes. Questionnaires will be conducted by telephone and immediately entered into Castor (data entry software) (Additional file 2).

**Table 2 Tab2:**
[figure not shown]
Study design and measurements

^a^After allocation, intervention group only

^b^Intervention group only

Visual acuity in the intervention group will additionally be measured with the online nurse-assisted eye screening after baseline/randomization.

Optometric status 12 months after baseline will include extensive optometric examination at the participants’ home with mobile equipment, including slit lamp examination for lens status, intraocular pressure (Icare), and fundus photography for thorough examination of the retina and optic nerve status (handheld Retcam). Any suspected deviation will be discussed with an ophthalmologist after which a patient will be referred. This measurement will be used for diagnostic purposes indicating whether we may have missed (latent) pathology in both groups but also to make sure that all participants will receive eye care after the study, if necessary.

### Outcome measures

Sociodemographic and disease characteristics, including reasons for receiving home healthcare, will be self-reported and based on medical records from the home healthcare organizations with the participant’s consent. Ophthalmic diagnoses and information on interventions will be obtained from the GP, optometrist, or ophthalmologist with the participant’s consent, for patients who received a referral.

#### Primary outcome

The primary outcome is a clinically relevant change of 2 lines or more (exceeding measurement error) on the Colenbrander-1 M visual acuity chart between baseline and 12 months follow-up.

Visual acuity will be assessed in both groups for both eyes separately at baseline and after 6 months and 12 months follow-up, by trained research assistants. These measurements will be performed in participants’ homes and will not be connected in any way to the nurse-assisted web-based screening, and outcomes will not be communicated with patients. Research assistants will be trained according to a strict protocol. The Colenbrander 1-M chart has an occluder attached to it with a rope of 1 m length. Participants will be asked to sit on a chair in front of the chart that is fixed on a music stand and adjusted to the participant’s height. The research assistant makes sure that there is sufficient light and no inappropriate reflection of light on the chart. Participants will be allowed to wear their own spectacles, except for reading addition. In glasses with varifocal lenses, participants will be asked not to look through the reading addition but straight over it. The occluder is equipped with a correction of + 1D. The number of letters read correctly will also be converted to logMAR visual acuity. The baseline and 6-month interpretations of the results of the vision-related measurements will not be shared with the participant and community nurse [41].

#### Secondary outcomes

The following vision-related outcomes will also be assessed: (1) average visual acuity change per eye in letters per participant between baseline and 12 months follow-up, including stenopeic visual acuity; (2) number of participants and eyes with baseline vision impairment (visual acuity 8/24 or lower with available optical correction) with clinically relevant progress of 2 lines or more; (3) optometric status 12 months after baseline; (4) vision-related quality of life with the EyeQ [42]; and (5) Amsler grid chart to detect symptoms of macular degeneration.

In addition, the following health-related measures will be assessed: (1) falling accidents and bone fractures with a shortened version of the “fall and fracture calendar” [7, 43]; (2) depressive symptomatology, measured with the Patient Health Questionnaire (PHQ-9) with nine questions corresponding to the Diagnostic Statistical Manual symptoms for major depressive disorder during the past 2 weeks. Good reliability and validity were shown using Rasch analysis [44, 45]; (3) health-related quality of life with the EuroQol 5-Dimension 5-Level questionnaire (EQ-5D-5L) which covers the dimensions mobility, self-care, daily activities, pain and discomfort, and anxiety and depression. Evidence indicated a reliable and valid instrument that describes health status [46, 47]; (4) well-being with the ICEpop CAPability measure for Older people (ICECAP-O) is a measure of capability in older people for use in economic evaluations. The ICECAP-O has good convergent validity with well-being measures [48]; (5) health literacy with the European Health Literacy Survey Questionnaire (HLS-EU-Q16). A high correlation (*r* = 0.82) was found with the general health literacy score of the HLS-EU-Q47 [49].

#### Cost-effectiveness

The Institute for Medical Technology Assessment (iMTA) Medical Cost Questionnaire (iMCQ) will be used to measure healthcare utilization at baseline and after 6 and 12 months of follow-up [50]. Standard costs for health care utilization from the Dutch costing manuals will be used [51]. In addition, the costs of the intervention will be measured, including treatment uptake after referral. Treatment uptake related to eye care will also be measured and valued for the control group. Medication use is valued using prices from Dutch Medical costs guidelines [52].

#### Process evaluation

For participants in the intervention group and community nurses, a process evaluation will take place at 6 months, by using a questionnaire. The RE-AIM framework (Reach, Effectiveness, Adoption, Implementation, and Maintenance) of the United Kingdom- Medical Research Council guidelines for process evaluations will be used. Three essential features of understanding the process through which outcomes are achieved will be identified: (1) context, (2) implementation, and (3) mechanisms of impact [31]. In addition, elements from the Telemonitoring Acceptance Framework [32] will be used to assess trust, behavioral intention, self-efficacy, performance expectancy, effort expectancy, social influence, facilitating conditions, technology anxiety, hedonic motivation, and user opinions regarding the nurse-assisted online eye-screening tool.

### Adverse events

All study-related adverse events (AEs) reported spontaneously by the subject or observed by the investigator or his staff will be recorded in Castor. Serious AEs (SAEs) will be reported through the web portal “ToetsingOnline” to the METC of Amsterdam UMC, which approves the protocol, within 7 days of first knowledge for SAEs that result in death or are life-threatening followed by a period of a maximum of 8 days to complete the initial preliminary report. All other SAEs will be reported within a period of a maximum of 15 days after the sponsor has first knowledge of the SAE. All SAEs will be followed until a stable situation has been reached or the SAE has resolved. Besides, the patient’s GP will be contacted.

### Data management

Data will be entered into Castor and converted into the statistical software packages SPSS, RStudio, and Stata. For each participant, a code (from 1000 to 3999) is used. A “key file” (in which these codes are linked with the patients’ names, addresses, and phone numbers) will be saved separately and will be deleted after the study has ended. Only the executive researchers will be able to access the key file. Data will be stored at Amsterdam UMC, location VUmc, computer network with a password in a folder that only the executive researchers can access. Medicine lists and signed application and consent forms will be kept in a locked cabinet in a locked room, only accessible to the executive researchers. Data will be stored for 15 years before they will be destroyed (Dutch law).

### Monitoring

Monitoring will be conducted by the clinical research bureau of Amsterdam UMC, location VUmc. The independent monitor will monitor the study data according to Good Clinical Practice. Informed consents will be checked in a selection of subjects. In addition, during the onsite monitoring, source data verification will be carried out. The intensity of this verification is related to the risk of the research, which is classified as negligible. The inclusion and exclusion criteria and the primary outcomes of the research will be checked. The monitor will also examine whether all (S)AEs have been adequately reported within the timelines as required by law and regulations.

### Statistical analysis

A table will be presented showing baseline demographic and clinical characteristics for each group.

To determine the validity of the questionnaires that are used within this study population, item response theory models will be performed. These models incorporate the characteristics of questionnaire items and responses, rendering a more accurate representation of the score on the latent construct, increasing the validity of the used questionnaires and the accuracy of the obtained results.

To determine effectiveness, linear mixed models (LMMs) will be used for continuous outcomes and logistic generalized estimating equation (GEE) analyses for dichotomous outcomes, given the longitudinal structure of the data. This will be based on intention-to-treat (i.e., all data will be included independent of completion of the intervention, including uptake after referral). We will use group (intervention vs. control), time, and the interaction between group and time as predictors. *P*-values less than 0.05 will be considered statistically significant.

The cost-effectiveness from a healthcare and societal perspective of eye screening compared to CAU will be determined based on the primary (incidence of clinically relevant changes in visual acuity) and secondary outcomes. Cost-utility will be determined with quality-adjusted life-years (QALYs) based on the EQ-5D-5L. Bias-corrected and accelerated bootstrapping with 5000 replications will be used to calculate 95% confidence intervals around the mean difference in total costs between the two groups for both perspectives. Incremental cost-effectiveness ratios (ICERs) and incremental cost-utility ratios (ICUR) will be calculated, as well as cost-effectiveness curves. Bootstrapping will be used to estimate the uncertainty surrounding the ICERs, which will be plotted graphically on cost-effectiveness planes. Cost-effectiveness acceptability curves will also be estimated. Costs for the consequences of not receiving ophthalmic treatment (for example, if the patient is not able to follow up on the referral because of other health problems) will be estimated and modeled. Findings will be integrated with published reports and literature to extrapolate the findings to a national level.

Guidelines by the ISPOR Task Force will be used for the budget impact analysis (BIA), i.e., relevant features of the health care system, access restrictions, anticipated uptake, and the use and effect of current and new intervention(s) will be considered. Also, the size and eligibility of the population, cost of interventions and treatment mixes (e.g., other ophthalmological or (mental) healthcare treatment), and changes expected in condition-related costs will be considered in the BIA. Sensitivity analyses will be performed using different scenarios from the perspective of decision-makers. Missing cost and effect data will be imputed using multiple imputation techniques according to the MICE algorithm.

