### Sample size

Taking into account a potential dropout of one-third, the sample size calculation revealed that we need 120 participants in the intervention group (receiving eye screening in addition to CAU) and 120 participants in the control group (receiving only CAU). A team of community nurses who provide care to patients in a specific geographical area will form a cluster. We aim to include 10 clusters in the intervention group and 10 clusters in the control group, both with 12 subjects each (Fig. 1), but this may vary in practice depending on the willingness of patients to participate within one cluster. Based on these numbers, we will achieve 82% power to detect a difference between the group proportions of 0.15, having a clinically relevant change of two lines or more in visual acuity (primary outcome measure). The proportion in the intervention group is assumed to be 0.05 under the null hypothesis and 0.20 under the alternative hypothesis. The proportion in the control group is 0.05. The test statistic used was the two-sided *Z*-test (unpooled). The intracluster correlation was set at 0.02 [33], and the significance level of the test was set at 0.05. Based on previous research in older populations [34], we expect that we need to invite approximately 1000 patients to include 240 participants. Loss to follow-up of one-third means that 80 participants (approximately 40 in both trial arms) are allowed to dropout during the course of the study in order to estimate the abovementioned effect, which seems reasonable based on previous studies [34] (Fig. 1).

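### Falls are repeatable events, but the stated models are a linear mixed model or a logistic GEE; a rate model would be a cheap improvement for this secondary outcome

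*Protocol article*

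**What the plan says.** In the protocol article, the Secondary outcomes section lists, among the health-related measures, "falling accidents and bone fractures with a shortened version of the" fall and fracture calendar. It does not say whether the endpoint is a number of falls, a rate, or any fall yes/no.

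The Statistical analysis section sets the effectiveness models by outcome type: "linear mixed models (LMMs) will be used for continuous outcomes and logistic generalized estimating equation (GEE) analyses for dichotomous outcomes". On the model terms it states: "We will use group (intervention vs. control), time, and the interaction between group and time as predictors". It names no Poisson, negative binomial or recurrent-event model, and no offset or exposure time.

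Four further statements bear on the point:
- Study procedures: "Measurements in both groups will take place at baseline (T0) and after 6 months (T1) and 12 months (T2) of follow-up".
- Sample size: "80 participants (approximately 40 in both trial arms) are allowed to dropout during the course of the study".
- Statistical analysis, on intention-to-treat: "all data will be included independent of completion of the intervention, including uptake after referral".
- Statistical analysis, on missing values: "Missing cost and effect data will be imputed using multiple imputation techniques according to the MICE algorithm".

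**The concern.** A calendar of falls naturally gives a number of events over a period of observation. A model for dichotomous outcomes can use it only after each interval is reduced to fell or did not fall, so a person with three falls in six months counts the same as a person with one. A model for continuous outcomes keeps the number but assumes normal errors for a small, skewed count with many zeros. Neither contains observed time.

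At stake is the precision of one secondary comparison. Falls are part of the article's rationale: the Discussion gives fewer falls and fractures as an example of how screening might lower costs, and the Statistical analysis section uses secondary as well as primary outcomes in the cost-effectiveness analysis. Repeat falls are information that this comparison would want to keep.

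**Working it through.** **No plan figure to reproduce.** The article states no fall rate, effect size or power for falls. Its 82% power concerns the visual acuity outcome and is not an input here. Every fall rate, dispersion and rate ratio below is an assumption.

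**Inputs from the article.** 120 participants per arm; one-third loss, about 40 per arm; assessments at 0, 6 and 12 months; two named model classes; predictors group, time and group by time.

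**Step 1: falls ignored by dichotomising.** Take a gamma-Poisson (negative binomial) count with mean μ per year and dispersion k, so that P(no fall) = (1 + kμ)^(−1/k).
- One 12-month indicator ignores the share 1 − P(any fall)/μ.
- Two 6-month indicators, which match the planned longitudinal GEE, ignore 1 − 2·P(any fall in 6 months)/μ.

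Worked case, μ = 1 and k = 1:
- Year: P(any fall) = 1 − 1/2 = 0.50, so 1 − 0.50/1 = 50% ignored.
- Half-years: P(any fall) = 1 − 1/1.5 = 0.333, so 1 − 2 × 0.333/1 = 33% ignored.

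Over μ = 0.5 to 1.5 and k = 0.5 to 2, the share is 28% to 67% for one yearly indicator and 16% to 51% for half-yearly indicators. The second range is the fair one for this plan.

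**Step 2: fit of a linear model.** The variance-to-mean ratio of the yearly count is 1 + kμ. It runs from 1 + 0.5 × 0.5 = 1.25 to 1 + 2 × 1.5 = 4. The variance therefore changes with the mean, and constant-variance normal errors are a poor description.

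**Step 3: power, against the longitudinal GEE.**

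*Simulation A.* 120 per arm, one-third leaving at a uniformly distributed time, 0.7 to 1.0 falls per person-year in controls, k = 0.5 to 2, rate ratio 0.6; six settings, 400 trials each, no team clustering.
- Negative binomial with offset, all observed time: 44% to 77%.
- Logistic GEE on completed 6-month intervals, one common group effect: 32% to 59%.
- Gap: about 10 to 18 points, with the rate model ahead in all six settings.

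The Monte Carlo standard error of one power estimate is at most √(0.5 × 0.5/400) = 2.5 points.

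*Simulation B.* Assumed rates, one-third dropout, completed 6-month intervals only, team-clustered standard errors.
- Count model over logistic GEE: about 5 to 12 points.
- Linear model on the counts: at most about 4 points below the count model.

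Taken together, dichotomising costs about 5 to 18 points. Treating the count as normal costs little.

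**Step 4: exposure.** If 40 of 120 per arm leave evenly over the year, observed time is (80 + 40 × 0.5)/120 = 83% of plan. An offset can use the partly observed intervals only if falls in them are recorded, which the article does not say.

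**The case against.** The strongest reply is that the model sentence is a general rule by type of outcome. It does not assign falls to either class, and the article never defines falls as a count. A journal article condenses the full protocol, and the coding of one secondary outcome may be settled there or in the analysis plan. If the endpoint is any fall per interval, logistic GEE is a legitimate match, only less efficient. A linear model on counts loses almost no power. The outcome is also weakly powered under any model: at an assumed rate ratio of 0.7 and 80 completers per arm divided by a design effect of 1 + 7 × 0.02 = 1.14 (the intracluster correlation borrowed from the primary outcome), even a negative binomial comparison has only 17% to 46%.

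Most of this stands and sets the severity. It does not remove the point: the article does fix its model classes and predictors, and a better-suited model costs almost nothing.

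A reader might infer more than the article supports:
- *That partial follow-up is thrown away.* The GEE is longitudinal, so a participant lost after 6 months still contributes the first interval. All data are to be included, and missing effect data are to be imputed.
- *That the falls comparison will be biased by arm.* The schedule is the same in both arms, the dropout allowance is about 40 in each, and the Discussion expects the 12-month optometric examination in both groups to make selective dropout in the control group less likely. Nothing points to a difference in observed time.
- *That falls are the main route to benefit.* The Discussion offers them as one example, after visual functioning, quality of life and other gains. Costs come from the cost questionnaire and intervention costs, and QALYs from the EQ-5D-5L; neither passes through the falls model.
- *That fractures suffer equally.* They are probably too rare per person for a yes/no analysis to lose much.

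**Conclusion.** The point holds as a minor efficiency improvement on a secondary outcome. The named models do not suit repeatable falls. The harm comes mainly from reducing falls to yes/no: about 16% to 51% of falls ignored with half-yearly indicators, and about 5 to 18 points of power lost against a count model. The linear alternative is a matter of fit, with at most about 4 points lost. The missing exposure term is a lesser gap, because the scheduled intervals are equal.

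These sizes rest on assumed fall rates, gamma-Poisson variation, rate ratio 0.6 for the power gaps, and dropout at the full one-third. No figure in the article is contradicted, and the primary outcome is not affected.

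**What to change.** Add one sentence to the Statistical analysis section: the number of falls will be analysed as a rate with a negative binomial model, with log observed time as offset and allowance for clustering by nurse team, and reported as a rate ratio with its confidence interval. If the shortened calendar records no dates, use the time between completed assessments as observed time. Keep any fall per interval by logistic GEE as a supportive analysis, and analyse fractures as yes/no.

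The cost is one additional model. It requires that the calendar records how many falls occurred and not only whether one did; the article does not state this, so it should be confirmed first.

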### Randomization

Teams of community nurses (clusters), which will participate in the cluster RCT, will be randomized to either the intervention (eye screening in addition to CAU) or control group (CAU). As there are differences in the number of participants a team is able to include, we will group participating teams into matched pairs on the basis of number of participants to prevent imbalance between the group sizes. One researcher (VR) will use Castor to randomize the clusters, by using block randomization. Randomization of the clusters will be stratified by home healthcare organization to stimulate regional heterogeneity and to equally divide the additional burden on the organizations. This will be done after the community nurse has invited patients to participate in the study. Due to the nature of the intervention, community nurses and participants cannot be masked. Research assistants, who will perform visual acuity measurements and administer questionnaires during the follow-up assessments, will be masked. Participants are asked not to disclose the nature of their treatment allocation during the follow-up assessments. The research team will regularly check whether a research assistant is still masked by asking to guess to which trial arm a participant is allocated. Allocation to the intervention or control group will be communicated with the community nurses by email by an unmasked researcher.

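### As written, the effectiveness models allow for repeated visits but not for clustering by the randomised nurse team

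*Protocol article*

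**What the plan says.** All references are to the protocol article.

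- **Randomization** makes the team the randomised unit: "Teams of community nurses (clusters), which will participate in the cluster RCT, will be randomized". The Discussion confirms that teams are randomised instead of individual patients, to prevent contamination.
- **Sample size** defines the cluster: "A team of community nurses who provide care to patients in a specific geographical area will form a cluster". It sets the numbers: "We aim to include 10 clusters in the intervention group and 10 clusters in the control group, both with 12 subjects each". It also makes an allowance for clustering: "The intracluster correlation was set at 0.02". Team sizes may vary in practice, and one-third dropout is allowed for.
- **Statistical analysis** specifies linear mixed models for continuous outcomes and, for binary ones, "logistic generalized estimating equation (GEE) analyses for dichotomous outcomes, given the longitudinal structure of the data". It adds: "We will use group (intervention vs. control), time, and the interaction between group and time as predictors". The threshold is p < 0.05.

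No section names the team as a random effect, as the GEE clustering unit or as the unit for a robust variance.

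**The concern.** The design sections treat participants in the same team as correlated. The analysis section gives one reason for its choice of models, the repeated measurements, and that reason does not cover the team. A statistician following it literally would make the participant the GEE subject and would fit a mixed model with visits nested in participants. Participants in one team would then count as independent of each other.

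In a cluster trial, the level at which observations are taken as independent is part of the design. It is more basic than a choice of working correlation or degrees-of-freedom method. If the team is ignored and outcomes do correlate within teams, standard errors of between-arm comparisons are too small. A result declared significant at 5% would then not carry that error rate, and the analysis would not match the design used for the sample size.

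**Working it through.** **Inputs** (Sample size): 10 teams per arm; m = 12 per team, or 8 after one-third dropout; 120 per arm, or 80 after dropout; ICC 0.02; two-sided alpha 0.05; unpooled Z-test; proportions 0.05 in both arms under the null, 0.20 versus 0.05 under the alternative.

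**The plan's own figure.** The variance sum is 0.20 × 0.80 + 0.05 × 0.95 = 0.2075. Power = Φ(0.15 / √(0.2075 × DE / n) − 1.96).

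- n = 80, DE = 1.14: Φ(2.759 − 1.96) = 78.8%.
- n = 120, DE = 1.22: Φ(3.266 − 1.96) = 90.4%.

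The stated 82% is not reproduced by either. That is a separate matter, and nothing below depends on it.

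**Effect of ignoring the team.** DE = 1 + (m − 1) × ICC. A test that ignores the team has a statistic with standard deviation √DE under the null, so:

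- interval width relative to the correct width = 1/√DE
- actual alpha = 2 × [1 − Φ(1.96/√DE)]

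| m | DE | Relative width | Actual alpha |
|---|---|---|---|
| 8 | 1 + 7 × 0.02 = 1.14 | 0.937 (6.3% too narrow) | 2 × [1 − Φ(1.836)] = 0.066 |
| 12 | 1 + 11 × 0.02 = 1.22 | 0.905 (9.5% too narrow) | 2 × [1 − Φ(1.775)] = 0.076 |

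As a sensitivity range, an assumed ICC of 0.01 (m = 8) to 0.05 (m = 12) gives alpha of 5.8% to 11.5%. With unequal teams, DE = 1 + [(1 + CV²)m − 1] × ICC. An assumed CV of 0.4 at ICC 0.02 gives DE 1.166 and alpha 0.070 (m = 8), or DE 1.258 and alpha 0.081 (m = 12).

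**Simulation check.** Beta-binomial data, 10 teams per arm, ICC 0.02, no treatment effect. The first value is for 8 per team, the second for 12.

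| Test | Event rate 5% | Event rate 20% |
|---|---|---|
| Unpooled Z-test, team ignored | 6.5%, 7.1% | 6.8%, 8.0% |
| Logistic GEE, robust variance by participant | 1.8%, 4.7% | 6.3%, 7.3% |
| Logistic GEE, robust variance by team, z reference | 2.7%, 5.2% | 7.4%, 7.7% |
| As above, variance × 20/18, t on 18 df | 0.7%, 2.6% | 4.6%, 4.4% |

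The GEE rows assume binary outcomes at 6 and 12 months and test the group effect at 12 months; at the 5% rate, runs with an empty cell were dropped. A separate simulation of a single-visit logistic Wald test that ignores the team agrees: 2.0% and 4.9% at a 5% rate, 6.1% and 7.2% at a 20% rate.

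**Reading the table.** The formula matches the Z-test closely. It does not carry over to the logistic Wald test at a 5% rate, where only 80 × 0.05 = 4 to 120 × 0.05 = 6 events per arm are expected and the test is conservative. At 20% the inflation appears as predicted.

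**Continuous outcomes.** In a mixed model whose target is group by time, a team effect that is constant over visits cancels from the contrast. What remains is variation between teams in change over time, for which the article gives no figure. The primary outcome is itself a change from baseline, so the stated ICC applies to it directly.

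**The case against.** The strongest reply is that the article is silent about the team and does not exclude it. The sentence on model terms lists predictors, that is, fixed effects. A random team intercept or a GEE clustering unit would not appear in such a list, and participant-level random effects are not mentioned either. Both model families can carry a team level. The authors clearly have clustering in mind, as the ICC and the Discussion show, and a statistical analysis plan that is not shown may specify it.

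This stands as far as it goes: a reader should not infer that the trial has decided to leave the team out. It lowers the confidence and the severity. It does not remove the mismatch, because the article gives a reason for its correlation structure and that reason omits the randomised unit.

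A second reply is that the inflation is modest at the planned ICC and is absent in simulation for a logistic Wald test at the plan's own 5% null rate. That is also correct. A reader might infer that the type I error exceeds 5% for the primary and all secondary outcomes; the documents do not support this, for the reasons shown in the working. The stated ICC belongs to the primary outcome only.

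Third, the choice of small-sample estimator is normally left to an analysis plan, and the article nowhere proposes an uncorrected team-level variance with a z reference. The correction therefore belongs in the remedy and is not a fault in the text.

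**Conclusion.** The point holds in a limited form. The stated effectiveness analysis does not account for clustering by team, although teams are randomised and the sample size assumes ICC 0.02. With equal teams of 8 to 12 at that ICC, ignoring the team makes intervals 6.3% to 9.5% too narrow and gives a nominal 5% test an actual level of about 6.6% to 7.6% by formula. Larger values need a higher ICC or unequal teams, which are assumptions here.

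The size for a given outcome is conditional. Sparse events can make the logistic Wald test conservative despite the omission, and continuous group-by-time effects are affected only so far as teams differ in their change over time. Conservatism from sparse data does not make a participant-level analysis valid for this design; it only happens to offset the error. The text should be corrected before analysis. Confidence is moderate, because the team may be specified in a document not shown.

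**What to change.** State in the Statistical analysis section that:

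- for the logistic GEE, the nurse team is the clustering unit, with a small-sample correction suited to about 20 teams, for example a Kauermann-Carroll or Mancl-DeRouen variance with a t reference on teams minus 2 (18 df);
- the linear mixed models include random intercepts for team and for participant within team, with a team-by-time term where the effect of interest is group by time, and Kenward-Roger or Satterthwaite degrees of freedom.

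Naming the team without a correction would not be enough: at a 20% event rate that test still rejected 7.4% to 7.7% of the time.

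**Cost.** Wording and standard software options; no new data. Standard errors rise by a factor of √1.14 = 1.068 to √1.22 = 1.105. Under the planned alternative, the 95% half-width for the risk difference goes from 0.100 to 0.107 (80 per arm) or from 0.082 to 0.090 (120 per arm). Moving from z to t on 18 df, with the design effect included, takes power from 78.8% to about 74% (80 per arm) or from 90.4% to about 87% (120 per arm). At event rates near 5% the corrected Wald test will be conservative (0.7% to 2.6% with the simple correction simulated above), so the authors should expect limited power if events are that rare.
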